**Staging of Dementia-FAST-Reisberg 1988**

| | | **Stage 1:** | **No impairment (normal function)** | | --- | --- | |  | Unimpaired individuals experience no memory problems and none are evident to a health care professional during a medical interview. | | **Stage 2:** | **Very mild cognitive decline (may be normal age-related changes or earliest signs of Alzheimer's disease)** | |  | Individuals may feel as if they have memory lapses, especially in forgetting familiar words or names or the location of keys, eyeglasses or other everyday objects. But these problems are not evident during a medical examination or apparent to friends, family or co-workers. | | **Stage 3:** | **Mild cognitive decline** *Early-stage Alzheimer's can be diagnosed in some, but not all, individuals with these symptoms* | |  | Friends, family or co-workers begin to notice deficiencies. Problems with memory or concentration may be measurable in clinical testing or discernible during a detailed medical interview. Common difficulties include:   - Word- or name-finding problems noticeable to family or close associates - Decreased ability to remember names when introduced to new people - Performance issues in social or work settings noticeable to family, friends or co-workers - Reading a passage and retaining little material - Losing or misplacing a valuable object - Decline in ability to plan or organize | | **Stage 4:** | **Moderate cognitive decline (Mild or early-stage Alzheimer's disease)** | |  | At this stage, a careful medical interview detects clear-cut deficiencies in the following areas:   - Decreased knowledge of recent occasions or current events - Impaired ability to perform challenging mental arithmetic-for example, to count backward from 100 by 7s - Decreased capacity to perform complex tasks, such as marketing, planning dinner for guests or paying bills and managing finances - Reduced memory of personal history - The affected individual may seem subdued and withdrawn, especially in socially or mentally challenging situations | | **Stage 5:** | **Moderately severe cognitive decline (Moderate or mid-stage Alzheimer's disease)** | |  | Major gaps in memory and deficits in cognitive function emerge. Some assistance with day-to-day activities becomes essential. At this stage, individuals may:   - Be unable during a medical interview to recall such important details as their current address, their telephone number or the name of the college or high school from which they graduated - Become confused about where they are or about the date, day of the week, or season - Have trouble with less challenging mental arithmetic; for example, counting backward from 40 by 4s or from 20 by 2s - Need help choosing proper clothing for the season or the occasion - Usually retain substantial knowledge about themselves and know their own name and the names of their spouse or children - Usually require no assistance with eating or using the toilet | | **Stage 6:** | **Severe cognitive decline (Moderately severe or mid-stage Alzheimer's disease)** | |  | Memory difficulties continue to worsen, significant personality changes may emerge and affected individuals need extensive help with customary daily activities. At this stage, individuals may:   - Lose most awareness of recent experiences and events as well as of their surroundings - Recollect their personal history imperfectly, although they generally recall their own name - Occasionally forget the name of their spouse or primary caregiver but generally can distinguish familiar from unfamiliar faces - Need help getting dressed properly; without supervision, may make such errors as putting pajamas over daytime clothes or shoes on wrong feet - Experience disruption of their normal sleep/waking cycle - Need help with handling details of toileting (flushing toilet, wiping and disposing of tissue properly) - Have increasing episodes of urinary or faecal incontinence - Experience significant personality changes and behavioral symptoms, including suspiciousness and delusions (for example, believing that their caregiver is an impostor); hallucinations (seeing or hearing things that are not really there); or compulsive, repetitive behaviours such as hand-wringing or tissue shredding - Tend to wander and become lost | | **Stage 7:** | **Very severe cognitive decline (Severe or late-stage Alzheimer's disease)** | |  | This is the final stage of the disease when individuals lose the ability to respond to their environment, the ability to speak and, ultimately, the ability to control movement.   - Frequently individuals lose their capacity for recognizable speech, although words or phrases may occasionally be uttered - Individuals need help with eating and toileting and there is general incontinence of urine - Individuals lose the ability to walk without assistance, then the ability to sit without support, the ability to smile, and the ability to hold their head up. Reflexes become abnormal and muscles grow rigid. Swallowing is impaired. | | | --- | --- | --- | --- | --- | --- | --- | --- | --- | --- | --- | --- | --- | --- | --- | --- | --- | --- | --- | --- | --- | --- | --- | --- | --- | --- | --- | --- | --- | |
| --- | --- | --- | --- | --- | --- | --- | --- | --- | --- | --- | --- | --- | --- | --- | --- | --- | --- | --- | --- | --- | --- | --- | --- | --- | --- | --- | --- | --- | --- |

APPENDIX 3 SCALES

# Name:­­____________Date:________________

# Id No:__________Rater______________

# MINI-MENTAL STATE EXAMINATION (MMSE)*

Please enter the scores for each component of the test. Following completion, sum the component scores to arrive at the total MMSE score.

| **Endpoint** | **Question/Task** | **Subject Score** | **Maximal Score** |
| --- | --- | --- | --- |
| **Orientation** | Say, “I am going to ask you some questions to test your memory. Some of these questions will seem easy, others more difficult. Please bear with me.” |  |  |
|  | 1. What year is it? |  | 1 |
|  | 2. Which season of the year is it? |  | 1 |
|  | 3. What month is it? |  | 1 |
|  | 4. What is today’s date of the month? |  | 1 |
|  | 5. What day of the week is it? |  | 1 |
|  | 6. What country are we in? |  | 1 |
|  | 7. What county are we in? |  | 1 |
|  | 8. What town are we in? |  | 1 |
|  | 9. What building are we in? |  | 1 |
|  | 10. Which floor are we on? |  | 1 |
| **Registration** | Say, “I am going to give you 3 objects to remember. I’ll ask you to repeat them back to me to make sure you have them down. Then I am going to ask you some other questions. In a few minutes, I’ll ask you to repeat the words again, so keep them in your mind.  The 3 words are: CUP, PENCIL, AIRPLANE.”  (Alternate words: SKY, CIGAR, JUSTICE) |  |  |
|  | Record the number of correct recalled words on first try (out of 3). If less than 3, repeat the words until the subject can repeat all 3. (Do this up to 6 trials.) |  | 3 |
|  | Record the number of trials needed for subject to recall all 3 words. Record number of trials here:_________  (DO NOT ADD THIS AS PART OF SCORE) | X | X |
| **Attention and Calculation** | Count backwards from 100 by 7’s. Stop subject after 5 subtractions (93,86,79,72,65). |  |  |
|  | Record the number of correct subtractions. |  | 5 |
|  | **ONLY IF** subject refuses to count, THEN ask subject to spell the word “world” backwards.  Number of letters in the correct order  (e.g., “dlrow”=5, “dlorw”=3) | DO THIS TEST ONLY IF COUNTING WAS NOT DONE  Score: | 5 |
| Recall | Say, “Please tell me the 3 words I asked you to remember a few moments ago.” |  |  |
|  | Record the number of correctly recalled words. |  | 3 |
| Language |  |  |  |
| Naming | Show the subject a wristwatch and ask him/her what it is. Record 1 point for a correct answer. |  | 1 |
|  | Show the subject a pencil and ask him/her what it is. Record 1 point for a correct answer. |  | 1 |
| Repetition | Say, “Repeat the following:  ‘No ifs, ands, or buts.’”  Record 1 point for a perfect response. |  | 1 |
| 3-stage command | Place a piece of paper in front of the subject. Say, “Take the paper in your right hand, fold it in half, and place it on the floor.”  Assign 1 point for EACH part correctly executed. |  | 3 |
| Reading | Print “Close your eyes” on a piece of paper and give it to the subject. Ask him/her to read it and do what it says.  Record 1 point if the subject closes his/her eyes. |  | 1 |
| Writing | Say, “Write a sentence, whatever you’d like.”  Record 1 point if the sentence has a subject and verb and makes sense. Correct grammar and punctuation are NOT necessary. |  | 1 |
| Copying | Say, “Please draw a copy of this picture, exactly as it is.”  Show the subject a picture of intersecting pentagons:  Record 1 point if all 10 angles are present, and 2 of them must intersect. Ignore tremor and rotation. |  | 1 |
| **TOTAL SCORE** | **SUM COMPONENT VALUES** |  | **30** |
|  |  |  |  |
| Level of Consciousness | Circle the level of consciousness that best describes the subject:  (There are no points assigned for this evaluation.) |  |  |
|  |  | Alert |  |
|  |  | Drowsy |  |
|  |  | Stupor |  |
|  |  | Coma |  |

| **Clinicians’ Global Impression of Change (CGIC) Guy 1976** |
| --- |
| - ·Also used as a general term for various impressionistic measures, rated by the clinician, based on interviews with or without a collateral source, with or without reference to mental status examination, and with or without reference to cognitive assessment results - Rated on 7 points: 1 = very much improved; 2 = much improved; 3 = minimally improved; 4 = no change; 5 = minimally worse; 6 = much worse; 7 = very much worse - An overarching but implicit assumption in its use is that clinicians are sufficiently skilled to make appropriate clinical inferences and assess meaningful change in patients. Therefore, there are only minimal guidelines; there are no instructions about the kind of interview to be conducted or the method for rating change. The instructions state: "As determined by the physician relative to baseline. Rate total improvement whether or not, in your judgment, it is due entirely to drug treatment. Choose ONE response ranging from 1, very much improved ; 2, much improved; 3, minimally improved; 4, no change; 5, minimally worse; 6, much worse; 7, very much worse" |

[figure not shown]

[figure not shown]

[figure not shown]

Appendix 4 accidental code break forms + adverse events

Accidental Codebreak Form

**PATIENT ID NO:**

**PATIENT NAME:**

**RATER NAME:**

DATE:

**Reason for code break**

**Action taken**

EUDRACT **2005-005087-93**

SITE

PATIENT NO

INITIALS **SAE**

**SERIOUS ADVERSE EVENT FORM (Page 1 of 2)**

**Should be faxed to [name] within 48 hours**

1. **1. This serious adverse event is defined as: tick “**√**” all boxes that apply):**

**1a** 􀀀 **Death 1e.** 􀀀 **Persistent or significant disability or incapacity**

# 1b 􀀀 Life-threatening 1f. 􀀀 Congenital abnormality/birth defect

**1c** 􀀀 **Requiring inpatient hospitalisation 1g.** 􀀀 **Other, (1h)specify_________________________**

**1d** 􀀀 **Prolonging inpatient hospitalisation**

**_________________________________________________________________________________________________**

1. **2. Subject Information:**

**2a Sex 2b Date of birth 2c Weight (kg) 2d Height (cm) 2e Ethnicity**

􀀀 **Male |__|__| / |__|__| / |__|__|__|__| |__|__|__| |__|__|__|** 􀀀 **Caucasian**

􀀀 **Female day month year** 􀀀 **Black**

􀀀 **Other, (2f) specify__________**

**__________________________________________________________________________________________________________**

**3. Adverse Event date of onset (1st symptom): 3a-d (a=date, b=day, c=month, d=year) |__|__| / |__|__| / |__|__|__|__|**

**day month year**

**Date when AE became serious (if different from onset date): 3e-h(e=date, f=day, g=month, h=year)**

**|__|__| / |__|__| / |__|__|__|__|**

**day month year**

**__________________________________________________________________________________________________________**

**4. Diagnosis or main symptoms(s) – Provide detailed description (attach additional sheets if necessary)**

**4a**

**_________________________________________________________________________**

# 5. Intensity: (5a)1. 􀀀 Mild 2. 􀀀 Moderate 3. 􀀀 Severe

**__________________________________________________________________________________________________________**

**6. Tests/ 6a 0.** 􀀀 **No**

**Laboratory 1.** 􀀀 **Yes attach all reports with normal ranges (where applicable) and date of result**

**__________________________________________________________________________________________________________**

**7. Study Drug: 7a Treatment No. |__|__|__|__|__| 7b Indication___________________________**

**Therapy Dates: 7c From: |__|__| / |__|__| / |__|__|__|__| 7eTo: |__|__| / |__|__| / |__|__|__|__| 7d** 􀀀 **If continuing**

**day month year day month year**

**At the time of the event provide: Unit Dose: ______7f_____ Frequency: ______7g___________ Route: ______7h______**

**Last Dose Date and Time (prior to event): |__|__| / |__|__| / |__|__|__|__|7i Time: |__|__| : |__|__| 7j**

**day month year**

**__________________________________________________________________________________________________________**

**Was the study drug administered 7k 0.** 􀀀 **No 7l If no, specify: _______________________________________**

**in accordance with the protocol? 1.** 􀀀 **Yes**

**__________________________________________________________________________________________________________**

**Was the study code broken ? 0** 􀀀 **No code should not be broken, unless necessary for subject treatment decision**

**1** 􀀀 **Yes If yes, specify reasons: ________________________________________________**

**SERIOUS ADVERSE EVENT FORM (Page 2 of 2)**

1. **8. Concomitant Drugs: (exclude those used to treat the event) repeat question group**

| **Drug** | **Indication**  **for Use** | **Daily Dose** | **Route** | Date of Administration | |
| --- | --- | --- | --- | --- | --- |
| **From 8e To 8i**  **Day Month Year Day Month Year** | | | | | |
| **8a** | **8b** | **8c** | **8d** | **8f 8g 8h**  **|__|__| / |__|__| / |__|__|__|__|** | **8j 8k 8l**  **|__|__| / |__|__| / |__|__|__|__|** |
| **|__|__| / |__|__| / |__|__|__|__|** | | | **|__|__| / |__|__| / |__|__|__|__|** | | |
| **|__|__| / |__|__| / |__|__|__|__|** | | | **|__|__| / |__|__| / |__|__|__|__|** | | |
| **9. Relevant Medical History: 9a**  􀀀 **No**  􀀀 **Yes, specify: 9b_______________________________________** | | | **10. Concomitant Diseases 10a**  􀀀 **No**  􀀀 **Yes, specify: 10b__________________________________________________** | | |

**11. Action taken with study drug:**

**11a**

1. **0** 􀀀 **No change**
2. **1** 􀀀 **Dosage changed Unit Dose:________11b__________ Regimen: _____11c_____________**
3. **2** 􀀀 **Drug temporarily discontinued**
4. **Date of reintroduction: 11d |__|__| / |__|__| / |__|__|__|__|**

**day month year**

1. **3** 􀀀 **Drug permanently discontinued**

**Did the event reappear after reintroduction? 0** 􀀀 **No Any use of 11f 0** 􀀀 **No**

**11e corrective**

**1** 􀀀 **Yes therapies? 1** 􀀀 **if yes, specify 11g__________**

**9** 􀀀 **NA**

**__________________________________________________________________________________________________________**

**12. Outcome: 12a**

**1** 􀀀 **Death Date: |__|__| / |__|__| / |__|__|__|__| Autopsy performed? 12c No** 􀀀 **0**

**12b Day Month Year Yes** 􀀀 **1 If yes, attach report**

**2** 􀀀 **Ongoing (persistence)**

**3** 􀀀 **Recovered with sequelae Date: |__|__| / |__|__| / |__|__|__|__|12d-g (recovery date) Specify sequelae: 12h**

**Day Month Year**

**4** 􀀀 **Recovered without sequelae Date: |__|__| / |__|__| / |__|__|__|__|**

**Day Month Year**

**9** 􀀀 **Unknown**

**Specify causes and circumstances of death: 12i__________________________________________________________________**

**__________________________________________________________________________________________________________**

**13a 13c**

**13. Relationship to Study Drug (assessed by the investigator) Relationship to disease:**

**0** 􀀀 **No 1** 􀀀 **Unlikely 2** 􀀀 **Possible 3** 􀀀 **Probably 4** 􀀀 **Definite 0** 􀀀 **No 1** 􀀀 **Unlikely 2** 􀀀 **Possible 3** 􀀀 **Probably 4** 􀀀 **Definite**

**Comment: 13b Comment: 13d**

**__________________________________________________________________________________________________________**

**14. Additional Comments: (if any)**

**14a**

**__________________________________________________________________________________________________________**

**15. Reporter’s Name and Position: Principal Investigator’s Name:**

**(if different from Investigator)**

**Signature: Signature:**

#### Date: |__|__| / |__|__| / |__|__|__|__| Date: |__|__| / |__|__| / |__|__|__|__|

#### Adverse Event Recording Form

**PATIENT ID NO:**

**PATIENT NAME:**

**RATER NAME:**

**DATE:**

Please tick the appropriate boxes for any adverse events and rate intensity (1=Mild, 2=Moderate, 3=Severe)( *Relationship to Study Drug rated: 1=No, 2=Unlikely, 3=Unknown, 4=Likely):

Please tick if reported by patient Present Intensity (1-3) Relationship to Drug*

Headache

Fatigue

Somnolence

Confusion

Hallucinations

Constipation

Vomiting

Dizziness

Gait abnormal

Seizures

Please describe any others:

Other 1

Other 2

Other 3

Comments + action taken

Appendix 5 Rescue Protocol

The rescue protocol will be activated if the patients behaviour deteriorates during the first 3 weeks at any time the patients responsible clinical team can withdraw the patient from the trial if clinically indicated. After 3 weeks rescue medication will not be permitted. The researcher/CSO will provide some site training on the rescue protocol which is compatible with good clinical practice based on the following:

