| **Outcome Measures** | **PRIMARY ENDPOINT**:  Change in CMAI at 6 weeks at 10mg twice daily dose – primary hypothesis 5 point difference in change score in favour of memantine. Intermediate assessment points at 2, 4, and 6 weeks.  **SECONDARY ENDPOINTS**:  Neuropsychiatric Inventory (NPI) 6+ 12 weeks, Clinical Global Impression (CGI), Severe Impairment Battery (SIB) at , 6 and 12 weeks, Change in CMAI at week 12, Quality of Life 6+ 12 weeks(QOL-AD), co-prescribed psychotropic medications, number of recorded incidents of aggression, and number of occasions rescue treatment utilised. NPI at 6 and 12 weeks  Respondent:  The difference between the memantine and the placebo groups at 6 weeks in the proportion of patients who are considered respondent. The respondent patient is a patient who had a 50% reduction in their total CMAI score. |
| **Statistical Methods** | The final analysis plan will be determined in consultation with the statistician but will involve the change in agitation inventory score from baseline to 6 weeks using the mean(SD). We may use standard survival analysis for remaining in trial and between-group ANOVA for clinical measures. |
| **Date of Final Version: 6.0 17.06.08** | |

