About 65% of patients with severe Alzheimer's Disease (AD) will have symptoms of agitation (Hope et al 1999). There are drawbacks associated with the currently available therapeutic interventions for agitation associated with Alzheimer's Disease. In a recent trial, in the group of patients with moderate to severe AD treated with memantine, there were fewer incidences of agitation (Doody et al 2005). There is therefore a clear need for shorter scale pragmatic trial in this area to consider the anti-agitation effect of memantine in the acute progressive phase in AD. It is hypothesized that memantine will be effective in reducing the symptoms of agitation associated with moderate to severe Alzheimer's Disease.

- 1. **Risks & Benefits**

Memantine has a favourable safety profile (Alva et al 2005; Doody et al 2005, Livingston and Katona 2005; Reisberg et al 2003). The current medication provision for agitation has a very limited evidence base and is not without morbidity issues for example over-sedation with some antidepressants and falls with antipsychotics. Memantine is a potential treatment with low morbidity even in comparison to the cholinesterase inhibitors. It may offer practical advantages over other drugs but there have been no RCTs which have looked at under 12 weeks.

1. **Objectives & Purpose**
   1. **Primary Objective**

To determine the efficacy of Memantine in the short term treatment of Agitation in Alzheimer’s dementia.

- 1. **Secondary Objectives**

1. To investigate the effect of Memantine on the subtypes of agitation such as verbal and physical aggression plus other sub-groups.
2. To investigate the effect of Memantine on other secondary outcome measures, namely activities of daily living, other BPSD symptoms specifically mood and psychosis, the need for rescue pharmacological intervention such hypnotics and antipsychotics, cognitive functioning**.**
3. To investigate what baseline factors predict clinical response.
4. To investigate whether there are any adverse effects of Memantine treatment in the study population.

5. To investigate the effect of Memantine on quality of life measures.

1. **Trial Design**
   1. **Description of Overall Trial Design and Plan**

A double-blind, randomised placebo controlled trial of Memantine for agitation in Alzheimer’s disease

164 Eligible Consenting subjects with AD and Agitation

Study Group

Randomisation

Baseline assessment

Placebo Group

2 week assessment

6 week assessment

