If there is a deteriorating patient;

-Withdraw (without breaking blind)

-or treat clinically rescue alternatives up to week 3 of trial only

Study Group

Rescue Group

Placebo Group

12 week assessment

4 week assessment

- 1. **Selection & Withdrawal of Study Population**

To be eligible for entry into the trial individuals must satisfy **all** of the inclusion criteria and **none** of the exclusion criteria.

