During the study patients will be allowed to continue taking stable doses of concomitant medicines including antidepressants, antihypertensives, anti-inflammatory drugs, atypical anti-psychotics, anticoagulants, laxatives, diuretics, hypnotics and benzodiazepines (Tariot et al, 2004). Concomitant administration of anti-parkinsonian medication will be permitted but stable dose and no patients on amantadine this is to avoid difficulties with PD stability as Memantine can have benefit in PD. Cholinesterase inhibitors will not be permitted unless patients have been stable on that medication for at least 3 months. The commencement of new psychotropic medications will not be permitted during the study except for rescue treatment as per guidelines (appendix 6) for managing the behavioural symptoms of dementia.

- - 1. **Consent / Assent**

The patient or patient’s legally authorized representative must provides written informed consent (with the patients assent) to participate in the trial

- - 1. **Subject Identification**

Patients assessed for eligibility (*prior to consent / assent for participation in the trial*) will be assigned an **identification number.**

Once randomised into the trial (*post consent / assent for participation into the trial*) a subject will be assigned a **randomisation code.**

- - 1. **Stopping Rules** There are two criteria for removal of subjects from the trial;

1. Unblinding will occur in the event of life-threatening change in physical state or need for urgent medical and/or psychiatric intervention as requested by the patient’s treating physician in consultation with the study team and study monitoring committee.

2. Drop out from the 12 week-phase of the study is permitted due to intolerable side-effects and clinically significant persistent uncontrolled agitation. This will be a primary end point but will not necessitate un-blinding for that patient.

If patients withdraw their consent for follow-up then, if at all possible, the reason for loss to follow-up should be ascertained and permission should be requested to use data collected already for the purposes of the trial. No further data will be collected on patients who withdraw from follow-up. They have the right not to give a reason for withdrawing from follow-up and also to request that no data is held on them.

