**Randomisation**

Memantine group

Placebo group

Week 1: 5mg once daily (+ placebo) (1 tablet twice a day)

(1 tablet twice daily)

Week 1: 1 tablet twice a day

Week 2: 5mg twice a day

10 mg nocte

(1 tablet BD)

Week 2: 1 tablet twice a day

Week 3: 5mg in the morning and 10mg in the evening

Week 3: one tablet twice a day

1 tablet BD

Week 4 – 10mg twice a day then continue

Week 4 – one tablet twice a day then continue

If patient responding and with no adverse effects, **continue** with this regime. If no improvement or a worsening in agitation occurs use rescue protocol if first 3 weeks if non effective or after 3 weeks then stop imp and use trust policy guidelines for BPSD according to clinical need.

12 weeks – This is an acute study and no data on long term effects on agitation, patients will stop treatment.

- - 1. **Intervention and control**

Patients randomised to the active drug arm will be prescribed active memantine. All the tablets supplied will be 5mg and 10 mg size. The dose regime will be as follows; week 1: 5mg in the morning-due to packaging for active Memantine arm this is will be placebo am and Memantine 5mg pm-Those on placebo arm will be 1 placebo twice daily ; week 2: 5mg twice daily; week 3: 5mg in the morning and 10 mg in the evening; week 4: 10mg twice daily.

Patients randomised to the placebo arm will receive placebo memantine. This will be identical in form (tablet size, shape and packaging) to the active drug. The titration regime will be as for the active drug.

If a serious worsening in agitation occurs, by clinical assessment the patient will be offered rescue therapy if this occurs during dose titration stage i.e. first 3 weeks (see appendix 5 for details of rescue therapy). If the serious worsening occurs after the titration phase or rescue therapy fails to work (if the patient is in the first 3 weeks of the study) the patient will be unblinded if appropriate. The patient will then be offered medication if appropriate by their consultant at a dose titrated according to clinical need and/or trust BPSD protocol (appendix 6). If worsening is attributed to memantine then the consultant will be advised to utilise the trust BPSD protocol.

Patients who have completed the trial will have trial medication stopped. Should agitation return then primary care/ local Community Mental Health Teams will treat as per standard practice for example as per trust guidelines- appendix 6.

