**Randomisation**

Memantine group

Placebo group

2 week assessment

4+ 6 week assessment

12 week assessment

Rescue treatment as per trust protocol up to **week 3**

- - 1. **Determining Response to Memantine**

Response to memantine will be determined as follows:

- - 1. Reduction in Agitation as measured by the CMAI will be the primary outcome measure. Thus it may be expected that if Memantine is effective in treating the agitation symptoms associated with AD, then more patients will remain in the trial in the treatment group than the placebo group and there will be a reduction in Agitation score on the CMAI.
    2. Secondary outcome measures include improvement in Neuropsychiatric inventory (NPI), Clinical Global Impression (CGI), Severe Impairment Battery (SIB), Quality of Life (QOL-AD) co-prescribed medications, number of recorded incidents of aggression, and number of occasions rescue treatment utilised.

All measures will be assessed at baseline.

The following scales will be completed for each patient at 2,4, 6 and 12 weeks;

a)Cohen-Mansfield Agitation Inventory

b)Mini-Mental State Examination

c)Clinical Global Impression of Change

The NPI , SIB and QOL-AD will be measured at 6 and 12 weeks.

We will allow follow up assessments to have a 7 days window from randomisation. Baseline assessments will occur prior to randomisation and follow up assessments after randomisation.

.

- - 1. **Unblinding Reporting**

Unblinding is defined here as anyone except the randomiser who is able to identify which group (active drug or placebo) a patient has been assigned to.

If either of the above are fulfilled, a Codebreak Form should be completed **as soon as possible** after the blind has been broken by the person for whom the blind has been broken. The form should be faxed to the Chief investigator and the original kept in a locked filing cabinet.

If the codebreak is due to a Serious Adverse Event, the Serious Adverse Event Form should be completed and processed in the usual way. If the codebreak is due to a non-serious adverse event, the Adverse Event Form should be completed and filed in the source notes.

- 1. **Statistical Methods**

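### The protocol contradicts itself on what rescue treatment is and when it is allowed; under the Appendix 5 rule the rescue count cannot answer the drug-need part of secondary objective 2

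*Protocol*

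**What the plan says.** Secondary objective 2 (section 5.2) asks, among other things, about "the need for rescue pharmacological intervention such hypnotics and antipsychotics", and sets no time limit. The rescue outcome in the Synopsis, repeated in section 6.6, is the "number of occasions rescue treatment utilised". Co-prescribed psychotropics stand beside it as a separate outcome.

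The rules for rescue are spread over several places in the Protocol:

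- Section 6.1, design diagram: "treat clinically rescue alternatives up to week 3 of trial only".
- Sections 6.5.2 and 6.5.3: rescue follows Appendix 5, during titration, with non-drug measures tried first where possible.
- Appendix 5: "After 3 weeks rescue medication will not be permitted". The one drug listed is trazodone, up to 150 mg a day, for behaviour that affects safety.
- Section 6.5.1, flowchart: if rescue does not work, "or after 3 weeks then stop imp and use trust policy guidelines for BPSD according to clinical need". The same chart sets the target dose: "Week 4 – 10mg twice a day then continue".
- Section 6.2.2, closing paragraph: new psychotropics are barred during the study "except for rescue treatment as per guidelines (appendix 6"), which is the trust BPSD protocol. No week limit is given.
- Section 6.6, flow chart: "Rescue treatment as per trust protocol up to" week 3.

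For analysis, section 6.7.5 plans a descriptive summary of co-prescribed psychotropics, and the Analysis Plan at the end of section 6.7 plans a survival analysis of remaining in the trial.

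**The concern.** There are two linked problems.

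First, the conduct rule is inconsistent. A site that follows section 6.2.2 may start a psychotropic under the trust guideline at any week and call it rescue. A site that follows section 6.5 and Appendix 5 may give only trazodone, only in weeks 1 to 3, and would treat anything later as a reason to stop study drug. The same prescription could be counted as rescue at one site and not at another.

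Second, if the more detailed rule (Appendix 5) is the one that governs, the rescue count does not match the objective it serves. The objective names hypnotics and antipsychotics; the rescue protocol lists neither. The objective has no time limit; the rescue window closes before the target dose starts.

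At stake is whether the trial can say anything comparative about the need for psychotropic drugs, which is one part of a secondary objective.

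**Working it through.** No figure in the plan needs to be reproduced here. The check is a comparison of texts plus one simple proportion.

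**Step 1. Which rule applies where**

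| Place in Protocol | Governing guidance | Drugs | Window |
|---|---|---|---|
| 6.1 diagram | not named | not named | to week 3 |
| 6.5.2, 6.5.3 | Appendix 5 | as Appendix 5 | titration, first 3 weeks |
| Appendix 5 | itself | trazodone only | first 3 weeks; none after |
| 6.2.2, closing paragraph | Appendix 6 | not shown (link only) | no limit stated |
| 6.6 flow chart | trust protocol | not shown | to week 3 |
| 6.5.1, 6.5.2 on later worsening | trust BPSD guideline (Appendix 6 in 6.5.2) | not shown | after failed rescue or after week 3; 6.5.1 has study drug stopped |

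The trust guideline is thus the rescue treatment itself in sections 6.2.2 and 6.6, but the step that follows rescue in section 6.5.

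**Step 2. Test cases**

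- A new antipsychotic in week 5 under the trust guideline: rescue under section 6.2.2; not rescue under Appendix 5 or section 6.5.
- A new antipsychotic in week 2 under the trust guideline: could be rescue under sections 6.2.2 and 6.6; not listed in Appendix 5.
- Trazodone in week 2: rescue under Appendix 5; its status under section 6.2.2 depends on a guideline whose content is not in the Protocol.

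**Step 3. What the count can hold under Appendix 5**

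- Hypnotics or antipsychotics: none listed, so none can be counted at any week.
- Any rescue drug in weeks 4 to 12: zero by rule.
- Trazodone in weeks 1 to 3: counted, so part of the need is captured.

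**Step 4. Share of follow-up in which rescue is open**

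- Window: 3 × 7 = 21 days.
- To week 6: 21 / 42 = 50%.
- To week 12: 21 / 84 = 25%.
- Scheduled days at 10 mg twice daily, to week 12: 84 − 21 = 63, of which 0 fall in the window.
- Follow-up visits at weeks 2, 4, 6 and 12: 1 of 4 falls in the window.

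**Step 5. What else could capture later need**

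- Co-prescribed psychotropics could record hypnotics and antipsychotics at any week. Section 6.7.5 states only a frequency summary, not tied to new starts or to agitation.
- Survival analysis of remaining in trial compares the arms, but section 6.2.5 allows drop-out for intolerable side effects as well as for uncontrolled agitation, so it does not isolate drug need.

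**The case against.** The best reply is that the mismatch depends on which rule is read as governing. Under section 6.2.2, rescue is a drug treatment with no week limit, and that could fit objective 2 well. This stands: the mismatch is a consequence of the Appendix 5 rule, not of every reading. It does not remove the contradiction, because section 6.2.2 can rescue the outcome only by overriding the explicit bar in Appendix 5.

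A second reply is that counting rules belong in a statistical analysis plan, which section 6.7.1 promises. That holds for the counting rule itself. It does not hold for conduct: an analysis plan cannot count treatment that the protocol bars, nor settle which drugs a site may give.

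A third is that later need is measured elsewhere. In part it is, as the last step of the working shows, and the Synopsis has patients withdrawn for worsening followed to 12 weeks. So a reader should not infer that drug need after week 3 goes wholly unrecorded.

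A fourth is that the operational text (sections 6.5.2 and 6.5.3 and Appendix 5) agrees and that sites are trained on it, so confusion may be limited. That is fair. The conflict in section 6.2.2 still matters, because that paragraph states which new drugs are allowed.

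A reader might also infer that the count mixes non-drug with drug occasions, since rescue begins with non-drug measures. No text says so, and objective 2 and Appendix 5 both use drug terms, so that remains a guess.

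**Conclusion.** The contradiction is plain from the text: section 6.2.2 conflicts with section 6.5 and Appendix 5 on both the guidance and the window, and section 6.6 conflicts on the guidance only. If Appendix 5 governs, the rescue count is zero by rule for 9 of 12 weeks (12 − 3) and never includes the drug classes that objective 2 names. That conclusion rests on the Appendix 5 reading and on trazodone being the only drug it lists. What the trust guideline contains is unknown from the Protocol.

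The size is modest: a conduct rule and one secondary outcome, worth correcting because the correction is cheap. Three stronger readings are not supported. The week-3 limit is not itself a fault; section 6.5.3 gives it a purpose, retention during titration. Nothing here shows an effect on the primary CMAI analysis. And the share of patients whose drug need would be missed cannot be stated, because the Protocol gives no rate at which need arises; the 50% and 25% above are shares of time, not of events. Nor does objective 2 name a dose, so the absence of full-dose days from the window is context, not a breach of the objective.

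**What to change.** Keep the week-3 rescue rule. Then:

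1. Correct the closing paragraph of section 6.2.2 and the flow chart in section 6.6 so that rescue means Appendix 5, weeks 1 to 3. State that the trust BPSD guideline (Appendix 6) applies only after failed rescue or after week 3, with study drug stopped, as the section 6.5.1 flowchart has it.
2. For the drug-need part of objective 2, compare between arms any new or increased psychotropic given for agitation, from randomisation to week 6 and to week 12, regardless of whether study drug was stopped.
3. Record drug, start date and reason at the existing visits at weeks 2, 4, 6 and 12.
4. Report how many of these starts followed unblinding, but do not exclude them. Exclusion would condition on an event after randomisation and remove many of the late starts that the outcome is meant to capture.

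The cost is two wording corrections, one reworded outcome and a medication question at visits already planned; current drugs and doses are already listed at baseline (section 6.3.9). No visit is added and clinical care under section 6.5 is unchanged. Patients who withdraw consent for follow-up will still be missing. There are two downsides: the outcome overlaps with co-prescribed psychotropics, and some late prescribing may be done unblinded, since section 6.5.2 allows unblinding when worsening occurs after titration or rescue fails.
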